### Interventions

2.6

#### Intervention group

2.6.1

Patients allocated to the intervention group will perform a MPEP during 6 months, with a frequency of 3 sessions per week, and approximately 45 to 50 minutes of duration each session, in addition to having to a MeDi.

The diet will follow the recommendations of a nutritionist in accordance with Davis et al^[49]^ and the main recommendations are ≥5 servings of vegetables/day; ≥3 servings of fruit/day; ≥3 serves of fish or seafood/week; ≥3 servings of legumes/week; ≥3 servings of nuts/week; ≥5 servings of bread or cereals/day; preferentially consume white meat, instead of red meat; 2 to 4 servings of poultry/week and ≤1 serving of red meat/week; 2 to 4 servings of eggs/week; and using olive oil as the main oil for cooking and dressing.

The design of the program is based on previous studies and recommendations where it is said that the intervention with different types of exercises has better benefits in elderly and frail people, as the European VIVIFRAIL program applied in frail community elders with cognitive decline.^[7,52,69–71]^ In other studies, for patients with osteoporosis, it is recommended to work primarily with progressive resistance training for all major muscle groups and balance exercises and it is not recommended to work with aerobic exercises.^[72,73]^ In addition, we have considered some proposed guidelines for the treatment of postmenopausal and senile osteoporosis,^[74]^ for the prevention of falls^[57,71]^ and we have also revised the guidelines from the position stand on Exercise and Physical Activity for Older Adults of the American College of Sports Medicine.^[75]^

The participation of the patients in the MPEP will be carried out in small groups of 5 to 8 people, which enables to have the benefits of collective work and, at the same time, allows the physiotherapist to supervise and instruct each patient at all times in a safe way. The distribution of patients in these small groups will be made homogeneously based on functional and cognitive impairment tests in the baseline assessment.

The structure of the sessions has been defined according to the recommendations of the American College of Sports Medicine,^[50]^ with 3 different parts: an initial warm-up, a main part, and a final cool-down and relaxation, as is shown in Figure 2. In this basic structure, traditional exercises of mobility, strength, balance, and coordination are included with the main objective of improving functional capacities. But, besides, games and some activities are also included with the aim, not only of improving the functional capacity but also of working the cognitive functions to reinforce the global effects of the MPEP.^[36]^ During the sessions, the physiotherapist will constantly promote social participation among the participants.

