### Sample size calculation

2.8

The sample size calculation has been made based on the potential modification of the score of the POMA-T. For this, we have considered the results obtained in the previous pilot study with 9 patients in a 1-month follow-up, and the preliminary trial with 72 participants with a ratio of 3:1 to the intervention group and the control one during 6 months. In the pilot study, the POMA-T was modified by 1.7 points. Then, in the preliminary trial, we accepted to calculate the sample size, as statistically significant, with a difference greater than or equal to 1.7 points with a dropTout rate of 15%.

In our current study, the sample size has been estimated to conduct a randomized controlled clinical trial with a 1:1 ratio between the 2 groups. In this new calculation, considering the data from the pilot study and some of the available data from the preliminary trial, we have reduced the minimal detectable change in the POMA-T to 1.5 points, with a standard deviation of 2 points and we have increased the drop-out estimated rate during the study to 33% by the difficulty to avoid intervention biases in the control group fundamentally. Therefore, with this, and accepting an alpha risk of 0.05 and a beta risk of 0.2 in a 2-sided test, 84 subjects are necessary, 42 in each group. The sample size calculation was made with the software “GRANMO sample size and power calculator” (7.12 version).

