### Statistical analysis

2.9

Data will be analyzed by using the IBM-SPSS software package (version 23.0). Descriptive data analysis will be reported by groups as means ± standard deviation for quantitative variables and as frequencies and percentages for qualitative variables. In the graphical representation, bar graphs by groups will be used for quantitative variables, and pie charts to represent categorical variables. The main change from baseline to 6 months will be calculated by using intention-to-treat analysis for each outcome measure.

Initially, for comparisons between groups at baseline, *t* tests or Mann–Whitney *U* tests will be used for continuous variables, depending on normality, which will be checked for each using the Kolmogorov–Smirnov test and normal probability box-plots, and the Chi-square test or Fisher test will be used for quantitative variables.

To analyze the efficacy of the multidomain intervention on the outcome variables, both in the primary and secondary outcomes, multivariate analysis of variance (MANOVA) will be applied with repeated measures (4 levels) to assess interactions between the factors and differences by categorical variables, with covariates, and pairwise comparisons post-hoc to determine whether there are significant differences between groups and within groups. The effect size for the MANOVA model will be calculated by the partial eta square (η^2^) that shows how much variance is explained by the independent variable.

We will carry out correlations with Pearson *r* coefficient to determine whether the values of 2 or more quantitative variables change in conjunction or are related in some of the moment of the study (time-factor in the statistical model).

For the analysis of the falls data, we will calculate the incidence rate during the study and the prevalence proportion by group and by sex at the end of the study (point prevalence). Subsequently, we will calculate the relative risk to estimate the magnitude of the association between the participation to the MPEP and falls, and indicate the likelihood of fall in the intervention group relative to the control group and also by sex.^[91]^

The statistical analysis will be conducted at a 95% confidence level. A *P* value < .05 will be considered to indicate statistical significance in all analyses.

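### Exercise is delivered in groups of 5 to 8 in one arm only, but the sample size and the MANOVA assume independent patients; any within-group correlation would make P values too small and lower power

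*Protocol article*

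**What the plan says.** Section 2.2 randomises patients individually. Under section 2.6.1 the intervention arm's programme "will be carried out in small groups of 5 to 8 people", and on how the groups are formed the protocol says: "The distribution of patients in these small groups will be made homogeneously based on functional and cognitive impairment tests in the baseline assessment". Section 2.6.2 gives controls usual care with no exercise group, so any clustering by group arises in one arm only.

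The sample size in section 2.8 is for "a randomized controlled clinical trial with a 1:1 ratio between the 2 groups". On POMA-T the protocol says "we have reduced the minimal detectable change in the POMA-T to 1.5 points, with a standard deviation of 2 points", adds a 33% drop-out rate, and concludes: "accepting an alpha risk of 0.05 and a beta risk of 0.2 in a 2-sided test, 84 subjects are necessary, 42 in each group". No ICC or design effect enters the calculation.

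Section 2.9 names the efficacy model: "multivariate analysis of variance (MANOVA) will be applied with repeated measures (4 levels"), with covariates that are not listed. The four levels are the visits, so the model handles correlation within a patient over time. It has no term for the exercise group.

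**The concern.** Patients in one exercise group share sessions for six months. The protocol treats that sharing as part of the treatment: the second main part of each session consists mostly of group games, the physiotherapist encourages social participation, and the Discussion expects group work to improve adherence. Each of these could make outcomes within a group more alike than outcomes between groups.

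In that case the intervention-arm mean varies more than the independence formula allows, while the control-arm mean does not. The standard error of the arm difference is then understated, the test rejects too often under the null, and a test that allows for the groups has less power than planned. The calculation leaves almost no reserve to absorb this.

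**Working it through.** **Inputs from section 2.8:** difference 1.5, SD 2, two-sided alpha 0.05, power 80%, drop-out 33%, allocation 1:1. **From section 2.6.1:** group size m = 5 to 8. For 42 patients that means 6 to 8 groups (42/8 = 5.25; 42/5 = 8.4). **Assumed:** ICC of 0, 0.01, 0.05 and 0.10, because the protocol gives none.

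**Step 1: reproduce the plan's figure.**
n per arm = 2 × (1.960 + 0.842)² × 2² / 1.5² = 27.9, so 28.
28 / 0.67 = 41.8, so 42 per arm and 84 in total. This matches exactly, under independence.
SE = 2 × √(2/28) = 0.535. Power = Φ(1.5/0.535 − 1.96) = 80.1%, or 78.7% with the t distribution.

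**Step 2: allow clustering in the intervention arm only, with total SD held at 2.**
Design effect DE = 1 + (m − 1) × ICC.
SE = 2 × √((1 + DE)/28).
Ratio of true to assumed SE: r = √((1 + DE)/2).
Type I error of the unadjusted test = 2 × (1 − Φ(1.96/r)).
Power of a test using the true SE = Φ(1.5/SE − 1.96).
Total N for 80% power: (2 × 2.802/1.5)² × (1 + DE) per arm, rounded up, divided by 0.67, rounded up, and doubled.

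| ICC | m | DE | r | Type I error | Power, 28 per arm | Total N for 80% |
|---|---|---|---|---|---|---|
| 0 | any | 1.00 | 1.000 | 5.0% | 80.1% | 84 |
| 0.01 | 5 | 1.04 | 1.010 | 5.2% | 79.4% | 88 |
| 0.01 | 8 | 1.07 | 1.017 | 5.4% | 78.8% | 88 |
| 0.05 | 5 | 1.20 | 1.049 | 6.2% | 76.3% | 94 |
| 0.05 | 8 | 1.35 | 1.084 | 7.1% | 73.5% | 100 |
| 0.10 | 5 | 1.40 | 1.095 | 7.4% | 72.6% | 102 |
| 0.10 | 8 | 1.70 | 1.162 | 9.2% | 67.6% | 114 |

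**Step 3: vary the conditions.**
- *Drop-out also shrinks the groups.* 5 × 0.67 = 3.35 and 8 × 0.67 = 5.36 completers per group. Type I error is then 5.7-6.3% and power 77.9-76.0% at ICC 0.05, and 6.4-7.6% and 75.6-72.0% at ICC 0.10.
- *Small-sample degrees of freedom.* The table uses normal quantiles, but the between-group variance comes from few groups. Simulating 6 groups of 5 with small-sample degrees of freedom gives power of about 72% at ICC 0.05 and 68% at ICC 0.10, against 76.3% and 72.6% in the table for m = 5.
- *All 42 per arm analysed, SD 2.* Power is 93.0% at ICC 0. At ICC 0.10 it is 88.1% (m = 5) or 84.1% (m = 8). Type I error is as in the table, because r does not depend on the number of patients.
- *Sorting alone.* In a simulation with 6 groups of 7, 33% random drop-out and a t test, groups were formed by baseline function with no shared group effect. Type I error was 5.2% with sorting and 5.1% without; power was 78.9% and 79.2%.

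**The case against.** The strongest objection is that everything depends on an ICC that the protocol does not give and that may be small. Exercises may be adapted to each patient (section 2.6.1), and the Discussion says small groups allow individual corrections. One physiotherapist appears to apply the intervention at a single centre, so a therapist or site effect would be common to all groups and would not create differences between them. At ICC 0.01 to 0.02 type I error is only 5.2-5.8% and power 79-77%. This stands: it supports the low end of the range and rules out stating the consequences as certain. It does not make the ICC zero, because peers, games and adherence are still shared.

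A reader might infer that forming groups by baseline function is itself what makes the test too liberal. It is not. Patients are randomised individually and sorted afterwards, and sorting alone left error and power unchanged in simulation. Only effects that arise during shared delivery matter.

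It can also be said that section 2.9 states intention-to-treat, and that with all 42 per arm analysed power stays above 80% up to ICC 0.10. That is correct, but the plan's own calculation rests on 28 completers, and the error inflation is the same either way.

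Finally, an analysis plan that is not shown might add a group term. But the protocol names its efficacy model and gives a complete sample size derivation, and both assume independence.

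**Conclusion.** The point holds conditionally and is a low-cost improvement. The intervention is group-delivered in one arm, and the stated calculation and model ignore it. If outcomes within exercise groups are positively correlated, P values are too small and power at 28 completers per arm is below 80%. The effect is slight at ICC 0.01 and becomes material from about 0.05: error 6.2-7.1% and power 76-74% there, 7.4-9.2% and 73-68% at 0.10, with power a few points lower again under small-sample degrees of freedom.

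A reader might go further and conclude that the P values are too small and the 80% is missed as a matter of fact. The document does not support that, since it gives no ICC and at ICC 0 nothing changes. The figures also assume a total SD of 2 in both arms, stable group membership and equal group sizes.

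**What to change.** 1. Record prospectively which exercise group each intervention patient attends, including any change of group. This may be hard to reconstruct later.
2. Alongside the MANOVA, prespecify a partially nested mixed model for POMA-T and the other primary outcomes: a random exercise-group effect in the intervention arm only, each control as a singleton, adjustment for the baseline value, and Satterthwaite or Kenward-Roger degrees of freedom. A sensitivity analysis is the minimum. Making it primary would replace the analysis that section 2.9 names, which is a larger change.
3. State in section 2.8 that 80% power assumes ICC 0, and give the power at ICC 0.01, 0.05 and 0.10.

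The cost is one recorded variable and some wording. The downsides are wider confidence intervals, a less favourable stated power, and a variance component estimated imprecisely from about 5 to 8 groups.

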**Figure 2 F2:**
[figure not shown]
Structure of sessions in the multicomponent physical exercise program.

As general premises, all exercises will be performed following a progression in dosage, intensity, and difficulty. This progression will be especially important in the exercises of strength, balance, and aerobic resistance, as we intend that initially there is an adaptation of the patient to the exercise, but later we will try to make that they always be a challenge to the patients.

During the sessions, the physiotherapist will give simple instructions to do the exercises, performing them before and simultaneously with the patients to help them to do the exercises by imitation, and giving them positive reinforcements constantly. The physiotherapist should try to ensure that the patients perform all the exercises as correctly as possible with the expected dose and intensity, although it is necessary to be careful and always consider possible exercises adaptations to the functional and cognitive state of the patient in a safe way.

The basic session of the MPEP will be structured into 3 parts (Fig. 2):

(1)Warm-up: The sessions begin with an initial warm-up from 5 to 10 minutes.

The patients will start with slow joint movements and mild stretches of main muscle groups. Depending on the functional capacity of the patients in each group, they can start seated on a chair, and later perform the exercises in standing position. The upper quadrant (upper limbs, shoulder girdle, head, and neck) could be worked in a sitting or standing position. The lower quadrant (lower limbs and trunk) will be worked in a standing position fundamentally, although sometimes it will also be possible working in a sitting position. Subsequently, mild aerobic training will begin where there are combined upper limbs movements, walking, pedal sitting, etc, always depending on the functional capacity of the patients and progressively increasing the intensity. Mild aerobic work can be alternated with mobility and stretching exercises.

(a)Main Part: The main part of the session will be divided into 2 with an approximate duration of 10 to 15 minutes each part.(b)Main Part 1: Some traditional exercises will be done to work on joint mobility but, fundamentally, strength exercises will be performed on the main muscle groups, alternating the work of the upper quadrant and lower quadrant muscles. In these strength exercises, the progression in the dose, intensity and difficulty should also be applied.

In addition, this part of the session includes moderate aerobic exercises that will be gradually increased, with different exercises as upper and lower limbs movements, walking, running, pedal sitting, indoor cycling, etc.

(a)Main Part 2 (ludic exercises): This part of the session will include different games, mainly group games, to improve agility, coordination and balance. Traditional and simple games, known to patients, will be carried out, with rules that are easy to understand and execute, and that allow to achieve the stated objectives.

For the main part, an extensive rehabilitation and fitness equipment will be used to perform the games. Exercises and games will be performed in different positions and surfaces and will be accompanied by a dual task activity (physical and cognitive) that also promote the social participation of patients.^[76,77]^

(1)Cool-down: In this final part of the session, mild aerobic exercises will be performed to progressively decrease cardiopulmonary and muscular activity. In static, standing, or sitting, patients will perform slow joint movements and mild stretches. Finally, preferably in a sitting position, patients will be instructed to perform relaxation exercises, trying to control breathing.

#### Control group

2.6.2

Participants allocated to the control group will receive usual care and continue with their life normally, without participating in a standardized exercise program, and with the possibility to receive physical rehabilitation when needed. They will be instructed to maintain their current physical activity level, and will have to carry out the evaluations provided for in the study at 1, 3, and 6 months, with a periodic telephone contact. When the control patients are admitted to the Center-AD, they will have the opportunity to participate in the MPEP as well as the intervention group.

### Outcome variables

2.7

In the baseline assessment, all variables will be measured including the sociodemographic variables. Later, all outcome variables will be measured at 1, 3, and 6 months (Fig. 1) and will be codified by the physiotherapist who will conduct the intervention. A summary of outcome variables in summarized in Table 1.

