### Recruitment/enrollment and allocating

2.2

Patients who request for admission to the Center-AD, and who meet the initial selection criteria will be invited to participate in the study. Patients and their families will receive oral and written information by the physiotherapist of the Center-AD, who will apply the intervention, and, after signing the informed consent (by the patient or the legal guardian), the patients will be cited to make the baseline assessment with a multidisciplinary evaluator team. They will be randomized and assigned to the study groups. The patients in the intervention group will be admitted, and in the control group, they will be placed on a waiting list for admission once their participation in the study has ended. The randomization will be undertaken by the physiotherapist and an independent member of the Direction of the Center, with no other involvement in the trial, by using a computerized randomization system (randomized.com). Into our research line, the data obtained in a pilot study and a preliminary clinical trial have helped to improve the design of our current study. See the flowchart in Figure 1.

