### Blinding

2.3

The multidisciplinary care team, with a neurologist, a neuropsychologist, and a physiotherapist, will perform all evaluations without knowing if the patients were enrolled and the group to which the patients have been assigned, and they will not have a relationship with the physiotherapist who applies the intervention. An independent researcher, who will not know the identification of the groups, will carry out the statistical analysis.

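### Section 2.7 has the unblinded treating physiotherapist code every follow-up outcome, which conflicts with the blinding and separation promised in section 2.3

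*Protocol article*

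**What the plan says.** Four statements in the protocol article bear on this point.

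- **Section 2.3 (Blinding), evaluators.** "The multidisciplinary care team, with a neurologist, a neuropsychologist, and a physiotherapist, will perform all evaluations without knowing if the patients were enrolled" or their group. The section adds that "they will not have a relationship with the physiotherapist who applies the intervention".
- **Section 2.3, analyst.** "An independent researcher, who will not know the identification of the groups, will carry out the statistical analysis".
- **Section 2.7 (Outcome variables).** After saying that all outcomes are measured at 1, 3 and 6 months, it says that they "will be codified by the physiotherapist who will conduct the intervention".
- **Section 2.2 (Recruitment/enrollment and allocating).** Patients and families are informed "by the physiotherapist of the Center-AD, who will apply the intervention". Randomization is then done by the physiotherapist (in context, the same one) together with a member of the Center's Direction who is otherwise uninvolved. On what follows allocation: "The patients in the intervention group will be admitted, and in the control group, they will be placed on a waiting list for admission".

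Section 2.1 labels the trial single-blinded. Section 2.7.1 names POMA-T, TUG and calcaneal ultrasound as the primary measures, and section 2.8 sizes the trial on POMA-T alone.

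**The concern.** Patients and therapist necessarily know who exercises and who waits, so the single-blind label rests on the evaluators and the analyst. Section 2.7 places between those two blinded roles the one trial worker who certainly knows the allocation, and it does so for every outcome at every follow-up visit.

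How much this matters depends on what coding means, and the article does not say. If it means turning observations into item scores, the blinding of the outcome is lost. If it means data entry, an unblinded person handles, queries or corrects values before analysis. If it means only attaching identifiers, the scores are untouched, but the treating physiotherapist still holds the link between results and patients.

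POMA-T is the most exposed measure. It is a 28-point scale built from judged items such as step symmetry, path deviation and trunk stability (section 2.7.1), and the planned difference is only 1.5 points. A small systematic tilt would look like a treatment effect, and no analysis could separate the two afterwards.

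A second, conditional route to unblinding comes from the design. During the trial one arm lives in the Center and the other does not. An evaluator who works there could infer the group from residence.

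**Working it through.** **1. The statements side by side**

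| Role | Knows the group? | Source | Handles outcomes? |
|---|---|---|---|
| Evaluators | No, as stated | 2.3 | Perform all evaluations (2.3) |
| Treating physiotherapist | Yes: delivers the program and takes part in randomization | 2.2, 2.7 | Codes all outcomes at 1, 3 and 6 months (2.7) |
| Analyst | No, as stated | 2.3 | Analyses (2.3) |

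Results have to pass from the first row through the second to reach the third. That sits against the separation between evaluators and treating physiotherapist in section 2.3, and it puts an unblinded step in a chain described as blind.

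**2. Where the evaluators work**

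Section 2.3 calls them a care team. Section 2.2 speaks only of the baseline visit: "the patients will be cited to make the baseline assessment with a multidisciplinary evaluator team". Neither section gives an employer, and no section says where follow-up visits are held. Section 2.2 does identify the treating physiotherapist as belonging to the Center. The residence route is therefore possible but not established.

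**3. Reproducing the plan's sample size**

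Inputs from section 2.8: difference 1.5 POMA-T points, SD 2, two-sided alpha 0.05, power 0.80, ratio 1:1, drop-out 33%.

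- n per arm = 2 × [SD × (1.960 + 0.842) / difference]² = 2 × [2 × 2.802 / 1.5]² ≈ 27.9, so 28.
- With drop-out: 28 / (1 − 0.33) = 41.8, so 42 per arm and 84 in total.

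This matches the stated 84. Power at 28 completers per arm is 80.1%.

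**4. Illustration of a scoring tilt (assumed values)**

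The article gives no estimate of rater or handling bias, so the shift *b* is an assumption shown over a range. The calculation uses a normal approximation for a two-group comparison of means, not the planned repeated-measures model.

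- SE = 2 × √(2/28) = 0.535 point.
- Rejection probability with no true effect = Φ(−1.96 + b/SE) + Φ(−1.96 − b/SE).

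| Assumed shift b (points) | b / 1.5 | b / SE | Two-sided error |
|---|---|---|---|
| 0 | 0 | 0 | 5% |
| 0.25 | 17% | 0.47 | 7.5% |
| 0.5 | 33% | 0.94 | 15.5% |
| 1.0 | 67% | 1.87 | 46% |

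The table shows how sensitive the test is to a tilt. It does not predict one for this trial.

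**The case against.** The strongest defence is that section 2.7 separates two acts, measuring and coding, while section 2.3 gives all evaluations to the blinded team. On that reading the treating physiotherapist only labels or enters results obtained by others, and coding after measurement cannot bias how POMA-T was scored. Someone who knows the allocation may also be needed to mask it for the blinded analyst. This part stands: the article does not show that the treating physiotherapist scores anything. What remains is that the word is undefined, that the task covers every follow-up outcome, and that masking group labels does not require the therapist to handle the results.

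A reader might go further and infer that the evaluators are the Center's own staff, that they will recognise residents, and that blinding therefore cannot hold. The article does not support this. It gives no affiliation and no place of assessment, and it expressly states that the evaluators are blind and separate from the therapist. It also says that they do not know who is enrolled, which may mean that they assess people outside the trial as well; residence alone would then not reveal the arm.

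Two further limits are fair. TUG is timed and ultrasound is device-measured, so the exposure to rater judgement falls mainly on POMA-T. And the error rates depend wholly on the assumed shift: 15.5% reflects a choice of 0.5 point and nothing in the document.

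**Conclusion.** The point holds as a conflict within the protocol. Section 2.7 assigns the coding of all follow-up outcomes to an unblinded person whom section 2.3 keeps apart from the evaluators. If coding includes scoring or data entry, the sizing outcome passes through unblinded hands before analysis. Whether evaluators could also infer the group from residence depends on facts that the article does not give, so that part is a conditional risk. It is not proof that blinding fails.

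No actual bias can be sized from the document. Under the stated SD of 2 and 28 completers per arm, assumed shifts of 0.25 to 1.0 point correspond to a two-sided error of about 7.5% to 46%. The sample size of 84 reproduces and does not change. The correction is worth making before follow-up data are collected, because such bias cannot be removed later.

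**What to change.** - **Section 2.7:** remove the treating physiotherapist from outcome coding. Have the blinded evaluator record raw results, including POMA-T item scores, under the study ID at each visit. Have coding and data entry done by someone blind to group, and say what coding consists of.
- **Sections 2.2, 2.3 and 2.7:** reconcile them, and state whether the evaluators work at the Center. The member of the Direction who helps randomize should not be given the coding task or code key as the text stands, because section 2.2 says that this person has no further role.
- **If the evaluators also care for residents:** drop the claim that they do not know the group, and report POMA-T as potentially unblinded.
- **Optional check:** record the evaluator's guess of allocation at 6 months.

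The cost is a change of wording and one task reassigned among existing people, plus one extra item at the last visit if the check is adopted. Arrangements for rooms and scheduling are operational detail that an article may leave to the full protocol.
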